### Exclusion criteria

Pregnant women in the second or third trimester of gestation; pregnant women with diagnosed thyroid disease; pregnant women without a telephone; pregnant women with communication difficulties (cognitive or sensory deterioration, language barrier); pregnant women who do not consent to participate in the study.

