### Description of the Study

The phases of the study are:

* **PHASE 1. Recruitment of primary care nurses (PCN)**: the project was presented to all the PCN within the study setting to recruit midwives interested in participating. Those who were interested in collaborating signed a document of commitment to participate in the study.

* **PHASE 2. Creation of the study groups (intervention-IG and non intervention-NIG) and midwife training programme**:

- The randomisation unit was the PCN. Using simple randomisation the centres distributed the IG and NIG at a proportion of 1:1.

- The formation of the participating midwives was carried out on 3 centralised work days during which the develpment of the study was explained in depth and they were given instructions on correct completion of the questionnaire on hygienic-dietetic habits in both a paper and electronic format. Each professional was assigned a support investigator to clarify any doubts which may arise during the study period. The objective of session was for the midwives to obtain sufficient training to avoid possible variability in the development of the study and in the collection and registration of data.

* **PHASE 3. Pilot study**: this was carried out in three randomly selected PCN with 30 pregnant women who were not included in the study in order not to affect the final results. This pilot study evaluated the study inclusion process of the pregnant women, data collection by paper and electronic questionnaire as well as the appointment circuit, referral and presentation of ioduria results.

* **PHASE 4. Recruitment of the pregnant women, initial evaluation and request for first ioduria (in IG and NIG)**:

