- Recruitment of the pregnant women: the pregnant women will be consecutively recruited from the women attending consultation to the midwife until the number of 25 women required by each PCN has been reached. Each midwife will know the number of women that they must recruit for the study. If a pregnant woman fulfils the inclusion criteria the midwife will explain the study to her and will ask for her participation. If the woman accepts she will be given the study information sheet in which the objectives and the characteristics are described and she will be asked to sign the informed consent form to thereby be included in the study. If the woman refuses to participate the reasons for this will be noted, as will the administrative, sociodemographic and obstetric variables with the aim of determining the profile of this type of pregnant woman.

- Initial evaluation of the pregnant women: on the first contact with the women and through an individualised interview the midwife will collect the following variables: administrative, sociodemographic, obstetric, those related to smoking, consumption of foods rich in iodine, iodised salt and iodised multiple vitamins. All the data will be reported in an electronic data collection file (EDCF) which will include the rule of internal coherence to guarantee the quality control of the data. Following the interview the midwife will make an educational intervention on the importance of good alimentation during pregnancy and the repercussions this has on maternal and foetal health, with special emphasis on the importance of the consumption of foods rich in iodine and iodised supplements. An informative sheet will also be provided on the importance of iodine during gestation.

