- Request for ioduria during the first trimester: the midwife will request an ioduria test and will explain the woman how to correctly collect the urine and will program the appointment for the second trimester visit of the pregnancy. On receipt of the ioduria results the midwife will note these in the EDCF. In cases in which iodine deficiency is detected the midwife will duly intervene, thus the reason for including the telephone number of the pregnant woman in the questionnaire. If iodine supplementation is indicated the administration will begin on collection of the first urine sample to avoid underestimation of the prevalence of iodine deficiency in the first trimester. Ioduria will be analysed using the Benotti&Benotti method performed in the laboratory of the Hospital Clinic of Barcelona.

* **PHASE 5. Group Education Intervention (only in IG)**: the coordinating midwives in each zone will be responsible for performing the educational workshops on hygienic-dietetic habits in the pregnant women in the intervention group. This workshop will be held in the first trimester since this is when organogenesis is produced and is therefore the time of greatest risk for the appearance of alterations in the development of the foetal central nervous system in cases of maternal iodine deficiency. The content of the educational workshop will be the same to avoid a variation in information and transmission of knowledge to the pregnant women, that is, to ensure receipt of homogeneous information by the pregnant women.

* **PHASE 6. Follow up (in IG and NIG)**: if a pregnant woman does not attend the appointment she will be called by telephone and if she cannot be contacted after 10 attempts she will be withdrawn from the study. The interview on hygienic-dietetic habits will be given in the second and third trimester appointments and determination fo ioduria will be requested. The reasons for participant withdrawal will be reported and a flow chart of the patients will be created throughout the study.

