## Discussion

One of the strengths of the present study is its design which is pragmatically oriented with respect to the needs of time and material resources.

Another strength of the study is the large number of midwives and patients involved, reinforcing the external validity of the data.

Since no register of women in the first trimester of pregnancy is available, selection of the study population can not be approached with a simple randomised sample but will rather be performed by consecutive sampling which could lead to a selection bias, the self-selection of the volunteer. To determine the possible presence of such a bias the administrative, sociodemographic and obstetric variables of the women who refuse to participate in the study will be analysed.

To increase the validity and reliability of the data collection of the hygienic-dietetic habits by individualised interview, the midwives have been especially trained in this task following a training session prior to initiation of the pilot study and a support investigator will be available to solve any doubts which may arise.

The difficulty in determining iodine intake through diet will be compensated by the determination of iodine levels in urine which is considered a good marker of iodine ingestion according to the WHO, UNICEF and ICCIDD [4,45].

To avoid the phenomenon of contamination which may appear when the intervention influences the subjects in the control group (frequent when the same work centre of the professionals belongs to different study groups), randomisation of the intervention will be performed by the PCN and not by study subjects. Although the unit of randomisation is the primary care unit, the intervention is given at the individual level and the outcomes are also measured at this level. The estimation of the design effect will be taken into account in all the main analyses.

Since participant losses and withdrawals randomly occur, any subject exclusion from the analysis may later affect group comparability. To preserve this all the patients included in the study will be evaluated according to the intention to treat principle and thus, all the patients will be analysed as pertaining to the group to which they were initially assigned independently of the treatment they have actually received.

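### Women are selected and consented by their centre's own midwives after allocation, with no concealment of arm described; the planned safeguards reduce the risk of arms that differ at entry but do not remove it

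*Protocol article*

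**What the plan says.** All references are to the Protocol article.

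- **Allocation and training come first.** In Description of the Study, Phase 2 is headed "Creation of the study groups (intervention-IG and non intervention-NIG) and midwife training programme". It reports both steps as done: "Using simple randomisation the centres distributed the IG and NIG at a proportion of 1:1", and "The formation of the participating midwives was carried out on 3 centralised work days during which the develpment of the study was explained in depth".
- **Recruitment follows, through the centre's midwife.** Phase 4 is written in the future tense: "If a pregnant woman fulfils the inclusion criteria the midwife will explain the study to her and will ask for her participation". The same midwife takes consent and conducts the baseline interview.
- **Sampling rule.** Phase 4 sets a quota for each centre: "the pregnant women will be consecutively recruited from the women attending consultation to the midwife until the number of 25 women required by each PCN".
- **Eligibility.** One exclusion leaves room for judgement: "pregnant women with communication difficulties (cognitive or sensory deterioration, language barrier").
- **Intervention.** Phase 5 is for the IG only, in the first trimester, and "the coordinating midwives in each zone will be responsible for performing the educational workshops".
- **Refusers.** Phase 4 records their reasons and their administrative, sociodemographic and obstetric variables. The Discussion names volunteer self-selection as the possible bias and says that "the administrative, sociodemographic and obstetric variables of the women who refuse to participate in the study will be analysed".
- **Analysis.** The Statistical analysis section plans a baseline comparison between the arms, a multilevel logistic regression on independent variables that were significant in bivariate tests, and adjustment for potential confounders and clinically relevant variables. It does not list these variables.

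**The concern.** Randomising centres makes the centres comparable in expectation. It does not do so for women who are invited and agree after the allocation is made. If the midwife or the woman knows the arm, joining means something different in each: in IG centres it brings a workshop, in non-intervention (NIG) centres it does not. IG centres might then enrol women who are more motivated, or more at ease in a group, and such women could have less iodine deficiency whatever the workshop does.

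The Discussion relies on intention to treat to preserve comparability. That principle protects the comparison from enrolment onward and cannot repair a difference that arises at enrolment. At stake is the between-arm comparison of deficiency, the contrast on which the sample size rests.

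**Working it through.** **1. The passages side by side**

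| Step | What the article states | What it leaves open |
|---|---|---|
| Allocation (Phase 2) | Centres randomised, reported as done | Who was told the result |
| Training (Phase 2) | Study explained in depth over 3 days | Whether arm was disclosed |
| Invitation and consent (Phase 4) | Done by the centre's midwife | Whether midwife or woman knows the arm; whether the workshop is mentioned before consent |
| Sampling (Phase 4) | Consecutive, to 25 per centre | No log of eligible women not invited is described |
| Refusers (Phase 4, Discussion) | Reasons and three groups of variables recorded and analysed | Whether by arm; no diet, smoking, supplement or ioduria data |
| Baseline (Statistical analysis) | Enrolled women compared between arms | Cannot show unmeasured differences |
| Model (Statistical analysis) | Bivariate selection plus confounder adjustment | First-trimester ioduria not named; Data Collection lists ioduria only as the dependent variable |

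The order of steps is explicit. Knowledge of arm at recruitment is neither stated nor excluded. PCT and midwife are among the administrative variables kept for refusers, so each refuser's arm can be recovered.

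**2. The plan's own sample size (Sample size calculation)**

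Inputs: 44% versus 29%, two-sided alpha 0.05, power 80%, loss 15%, intracluster correlation 0.05, 25 women per centre.

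- Two proportions with continuity correction: 173.6 per arm. Allowing for loss: 173.6 / 0.85 = 204. This matches the stated 204.
- Design effect: 1 + (25 − 1) × 0.05 = 2.2.
- 408 × 2.2 = 897.6, so 898 women; 898 / 25 = 35.9, so 36 centres.

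The stated figures reproduce and are not disputed. The effective number per arm after loss and clustering is 204 × 0.85 = 173.4.

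**3. Illustration of size (assumed inputs; the documents give none)**

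Spurious difference = gap in deficiency between two types of women × difference in their share of each arm.

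- 0.20 × 0.10 = 0.02
- 0.20 × 0.20 = 0.04, which is 4/15 = 27% of the target difference

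Now suppose there is no workshop effect, that a shift b carries through to the outcome, and that there is no adjustment. With n = 173.4, compare 0.44 with 0.44 − b:

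rejection rate = Φ((b − 1.96·SE0)/SE1) + Φ((−b − 1.96·SE0)/SE1)

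SE0 is the pooled and SE1 the unpooled standard error. For b = 0.04: SE0 = √(2 × 0.42 × 0.58 / 173.4) = 0.0530 and SE1 = √((0.44 × 0.56 + 0.40 × 0.60) / 173.4) = 0.0530. The rate is Φ(−1.21) + Φ(−2.72) = 0.117.

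The last column takes a true 15-point effect with the shift running against the intervention, so it compares 0.44 with 0.29 + b.

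| Shift b (points) | Two-sided rejection rate, no effect | Power for a true 15 points, shift against the intervention |
|---|---|---|
| 0 | 5% | 83% |
| 2 | 7% | 71% |
| 4 | 12% | 56% |
| 5 | 16% | 48% |
| 10 | 48% | 15% |

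Power at zero shift is 83%, not 80%, because the test here has no continuity correction.

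**The case against.** The strongest reply is that the article may be silent only because it condenses a fuller protocol. It nowhere says that midwives were told their arm. Recruiting midwives do the same tasks in both groups, and coordinating midwives run the workshops, so masked recruitment fits the text. Only one information sheet is mentioned, and no passage says that women hear of the workshop before agreeing. This stands: a reader might infer that recruiters knew the arm, but the documents support only that no concealment is described. The Discussion justifies randomising centres by the risk of contamination when professionals at one work centre belong to different groups. That treats professionals as belonging to an arm and makes knowledge of it plausible, without proving it.

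A reader might also infer that refusers will be compared with participants only in a pooled analysis. The text says neither pooled nor by arm. Reasons are recorded, a flow chart is planned and the cluster CONSORT guide is cited, so a split by arm may well be done.

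The safeguards in the plan count. Consecutive recruitment to a fixed number limits a midwife's discretion. The baseline comparison would show measured differences among enrolled women, and adjustment would partly correct them. What these do not cover is differential refusal, selective invitation (which cannot be checked without a log of uninvited women) and unmeasured motivation. The general promise to adjust does not commit the model to first-trimester ioduria.

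Finally, the illustrated shift rests on invented inputs and assumes that the gap persists undiminished, although both arms receive individual education and midwives act on detected deficiency. That is fair, and the figures should be read only as a scale.

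**Conclusion.** The concern holds in a limited form. Allocation and training precede recruitment by the centres' own midwives, no concealment at that step is described, and only one arm is offered a workshop. Entry could therefore differ by arm. The planned measures reduce this risk without removing it, and two cheap protections are not fixed: a by-arm look at refusal, and first-trimester ioduria as a covariate.

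The documents do not show that the arms are imbalanced or that the result is biased. The 2 to 4 point shift, with an error rate of about 7% to 12%, depends on the assumed 20-point gap and 10 to 20 point imbalance, on no adjustment, and on full persistence to the outcome. The direction is also unknown.

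A reader might infer that the centres should be re-randomised with stratification. That would not follow: allocation is reported as done, and stratifying centres does nothing about selection of women afterwards.

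The change is worth making because it protects the main contrast at little cost. Confidence is moderate, since knowledge of the arm is inferred.

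**What to change.** **Where recruitment is still open** (the stated study period is 2007 to 2010):
- Use the same study explanation and information sheet in every centre.
- Have the coordinating midwives invite IG women to the workshop only after consent, first interview and first urine are logged, still within the first trimester as the plan requires.
- Keep recruiting midwives unaware of the arm where feasible.

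**In all cases:**
- State who knew the arm at recruitment.
- Compare between IG and NIG the numbers approached (where recorded), refusal rates, reasons and refuser profiles, with PCT as the cluster. The PCT code already recorded for refusers makes this possible.
- Prespecify first-trimester ioduria, taken before the workshop, and the sociodemographic variables as covariates in the multilevel between-arm model for second- and third-trimester deficiency, whatever their bivariate significance.

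**Cost:** a small change in logistics using staff already in the plan, one extra table and a fixed covariate list. The analysis steps need no new data. Fitting the invitation between the first urine and the end of the first trimester needs some care. Concealment may fade as women talk to their midwives, and unmeasured differences would remain.

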## Background

Iodine is a fundamental micronutrient for the organism which should be regularly administered through foods. Its function is essential for the synthesis of thyroid hormones which in turn act on the different organs and systems of the organism especially in the development of the central nervous system (CNS) from the earliest stages of embryonic and foetal development.

The ingestion of iodine depends on the type of foods consumed, their origin and preparation. Depending on the geographical area, products from the earth may have scarce iodine content. However, foods of marine origin are rich in this micronutrient [1]. In addition, it should be taken into account that foods lose iodine during their preparation: 20% is lost on frying, 23% on baking and 58% on boiling [2]. Some studies have shown that the iodine content of cows' milk differs according to what the animals are fed [3].

All these factors and alimentary habits make it difficult for the daily iodine requirements of the population to be covered through diet. Moreover, iodine is not stored in the body and must therefore be continually replenished. In normal conditions there is equilibrium between iodine intake and urinary elimination, and determination of iodine in urine (ioduria) constitutes a good indicator of iodine intake [4], with assessment of ioduria in a casual urine sample providing adequate information on the nutritional status of iodine [5].

During pregnancy there is an increase in thyroid hormone requirements due to the physiological modifications produced in response to the metabolic demands of pregnancy. This increase can only be achieved by a proportional increase in hormone production which directly depends on the availability of iodine in the diet. Moreover, gestation produces a physiological increase in the elimination of iodine in the urine because of a rise in glomerular filtration. In cases with an underlying deficit in iodine these modifications of pregnancy may not be compensated leading to failure of the mechanisms of adaptation. It is therefore very important to increase iodine intake from the beginning of gestation and even beforehand if possible, similar to the recommendations of supplementation of folic acid. The thyroid hormones available for embryonic and foetal tissue during the first trimester of gestation depend exclusively on maternal hormones and thus, a deficit in maternal iodine can have negative repercussions on prenatal development [6].

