### Sample size calculation

The sample size has been calcuated by multipying the size of a randomized simple design by the design effect. For the simple randomized design an alpha error of 0.05 and a beta error of 0.20 in a bilateral contrast are considered, requiring 204 pregnant women in the intervention group and 204 in the non intervention group to detect a difference greater than or equal to 15% in the prevalence of iodine deficiency between the two. After extensive review of the literature on group educational interventions in a pregnant population, the investigative team [37-40] considered that the intervention to be undertaken in the intervention group will achieve an improvement of at least 15% in hygienic-dietetic habits and thus in the levels of ioduria. A proportion of iodine deficiency of 44% in the non intervention group is assumed as indicated by studies performed in populations in the Pyrenees and the coast of the Maresme, areas near the study setting [18]. A loss to follow up of 15% has been estimated. Using an intracluster correlation coefficient of 0.05 [41-43], and based on an average of 25 pregnant women per PCT, the design effect is 2.2. Therefore, 898 pregnant women and 36 PCT are needed.

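### Phase 4 places iodine education and a leaflet before the first-trimester urine request, so observed first-trimester deficiency may be too low by an unknown amount

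*Protocol article*

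**What the plan says.** All references are to the protocol article. Under Description of the Study, Phase 4 applies to both arms and lists three steps for the first contact.

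- An individual interview on diet, iodised salt, iodised multivitamins and smoking.
- Education: "Following the interview the midwife will make an educational intervention on the importance of good alimentation during pregnancy and the repercussions" for mother and child. The sentence goes on to stress iodine-rich foods and iodised supplements, and the woman also receives an information sheet on iodine.
- The urine request: "the midwife will request an ioduria test and will explain the woman how to correctly collect the urine".

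The article gives neither a day of collection nor a maximum interval from the visit. It does say that supplementation, where indicated, starts on collection of the first sample, and gives the reason: "to avoid underestimation of the prevalence of iodine deficiency in the first trimester".

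The Background says that "iodine is not stored in the body and must therefore be continually replenished", that intake and urinary elimination are normally in balance, and that a casual urine sample is adequate. Sample size calculation expects that the group education "will achieve an improvement of at least 15% in hygienic-dietetic habits and thus in the levels of ioduria".

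General objective 2 is the prevalence of ioduria below 150 μg/L, and its associated factors, in the first three months. Phase 5, the group workshop for the intervention group only, also falls in the first trimester.

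**The concern.** The protocol treats urinary iodine as a marker of current intake and expects education to raise it. In the listed order, however, women are advised to take more iodine before the sample that gives first-trimester prevalence is requested. If days pass between advice and collection, some women may already have changed what they eat, switched to iodised salt or begun a supplement themselves. Observed prevalence would then be lower than prevalence at presentation.

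Two results depend on this sample. The first is first-trimester prevalence under general objective 2. The second is any analysis that pairs the first interview with the first urine: the associated-factors analysis, and the questionnaire validation in Phase 7 so far as it uses first-trimester values. The interview records intake before the education, whereas the urine may reflect intake after it.

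**Working it through.** **Order and safeguards, by route**

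| Route by which ioduria could rise before sampling | Promoted by the education or leaflet? | Closed by the protocol? |
|---|---|---|
| Supplementation that is indicated | Yes | Yes, start tied to collection of the first urine |
| Supplements the woman starts herself | Yes | Not stated |
| More iodine-rich food | Yes | Not stated |
| Switch to iodised salt | Plausibly, as part of advice on iodine | Not stated |

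The downward direction follows from the protocol's own premises: ioduria follows intake, and education improves intake.

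**The plan's own figures**

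Inputs from Sample size calculation: "an alpha error of 0.05 and a beta error of 0.20 in a bilateral contrast are considered"; "A proportion of iodine deficiency of 44% in the non intervention group is assumed"; the aim to "detect a difference greater than or equal to 15% in the prevalence of iodine deficiency"; 15% loss; intracluster correlation 0.05; 25 women per team.

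- Simple design: 44% against 59% gives 173 per group (arcsine) or 174 (pooled normal). Inflated for loss, 173/0.85 = 203.5, so 204, which matches the plan. For 44% against 29%, the pooled normal formula gives 161, or 174 with continuity correction, and 174/0.85 = 204.7, so 205. The stated 204 is therefore reproduced to within rounding.
- Design effect: 1 + (25 − 1) × 0.05 = 2.2.
- Total: 2 × 204 × 2.2 = 897.6, so 898; 898/25 = 35.9, so 36 teams.

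The order of steps changes none of these figures. They serve below only as a yardstick.

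**Sampling error of a first-trimester prevalence**

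Half-width = 1.96 × √(p(1 − p) × design effect / n) = 1.96 × √(0.44 × 0.56 × 2.2 / 898) = 1.96 × 0.0246 = 0.048, or 4.8 percentage points.

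**Possible bias**

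Let s be the share of truly deficient women whom the education moves above 150 μg/L before sampling. The documents give no value for s, so these values are assumptions. Observed prevalence = 0.44 × (1 − s), and bias = 0.44 × s.

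| s (assumed) | Observed prevalence | Bias (points) | Against 4.8 |
|---|---|---|---|
| 0% (for example, same-day urine) | 44.0% | 0 | none |
| 5% | 41.8% | 2.2 | below |
| 10% | 39.6% | 4.4 | below |
| 15% | 37.4% | 6.6 | above |

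Break-even: 0.048/0.44 = 0.109, so the bias exceeds the half-width only when s is above about 11%.

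As an outer marker, a fall of the full 15 points would show a true 44% as 29%. That is the effect the plan assumes for the group workshop, and nothing in the article transfers it to a short individual talk.

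**The case against.** The strongest reply is that the article does not say the urine is collected later. It says the test is requested and the collection explained; same-day collection fits that text, and the Background accepts a casual sample. On that reading no diet change has had time to occur. Collection logistics are also detail that a journal article may leave to the full protocol, and the pilot study did test the circuit for appointments and ioduria results. This stands as far as size is concerned: a reader might infer that the sample is known to underestimate deficiency, and the article does not support that. It does not remove the point, because the visit order is stated and nothing in the article secures sampling before the advice.

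A reader might also infer that the treatment comparison is biased. It is not, on this ground alone, because Phase 4 education is given in both arms. Nor does the article show that intervention-group urine is taken after the workshop. The numbering of the phases suggests the opposite; only an explicit rule is absent. The analysis section does not name baseline ioduria as a covariate, so harm to a baseline-adjusted comparison would be speculation.

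Finally, prevalence is not confined to this one sample. The Abstract speaks of deficiency during pregnancy, and interview and ioduria are repeated in the second and third trimesters. The validation text does not restrict itself to the first sample either. This narrows the consequences to first-trimester prevalence and first-trimester pairings.

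**Conclusion.** The point holds as a risk that the stated visit order creates and that a small change would remove. The protocol names underestimation of first-trimester deficiency as something to avoid, yet blocks only the indicated-supplement route.

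The size cannot be derived from the article. It is near zero with same-day sampling. It reaches 2.2 to 6.6 points if 5% to 15% of deficient women cross the cut-off first, against a half-width of 4.8 points. That range is an assumption. So is using 44% as true first-trimester prevalence, since the plan gives it as the non-intervention proportion for the sample size. The half-width also rests on all 898 women supplying a first sample and on a design effect of 2.2.

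The sample size and the between-arm comparison are not called into question.

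**What to change.** - In Phase 4, state that the casual first urine sample is collected at the first visit, before the education and the leaflet.
- Where that is not possible, record the sampling date and the number of days since the education. The variables listed under Data Collection include a general collection date but none specific to the urine.
- Report first-trimester prevalence from samples taken before the education, and add the remaining samples in a sensitivity analysis.
- State explicitly that the first urine in the intervention group is collected before the workshop.

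The content of the education and the rule on supplementation are left as they are. The cost is the minor inconvenience of sampling at the visit, a change of wording in the visit order, and one extra date field.
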